## Abstract

**Background:**

The CARTS study is a multicenter feasibility study, investigating the role of rectum saving surgery for distal rectal cancer.

**Methods/Design:**

Patients with a clinical T1-3 N0 M0 rectal adenocarcinoma below 10 cm from the anal verge will receive neoadjuvant chemoradiation therapy (25 fractions of 2 Gy with concurrent capecitabine). Transanal Endoscopic Microsurgery (TEM) will be performed 8 - 10 weeks after the end of the preoperative treatment depending on the clinical response.

Primary objective is to determine the number of patients with a (near) complete pathological response after chemoradiation therapy and TEM. Secondary objectives are the local recurrence rate and quality of life after this combined therapeutic modality. A three-step analysis will be performed after 20, 33 and 55 patients to ensure the feasibility of this treatment protocol.

**Discussion:**

The CARTS-study is one of the first prospective multicentre trials to investigate the role of a rectum saving treatment modality using chemoradiation therapy and local excision. The CARTS study is registered at clinicaltrials.gov (NCT01273051)

## Background

Colorectal cancer is the third most common malignancy in the Netherlands with more than 10.000 new patients of whom approximately one third have rectal cancer.

Total Mesorectal Excision (TME) using sharp nerve-sparing dissection, instead of blunt resection, reduced the 5-year local recurrence rate from up to 45% to less than 10% in patients with rectal cancer [1,2]. The use of this nerve-sparing technique results in lower rates of sexual dysfunction and urinary incontinence, but these complications are still common after TME [3]. Addition of preoperative radiotherapy to surgery resulted in a significant better local control for resectable rectal cancer. Five-year local control rate using a short course (5 × 5 Gy) of pre-operative radiotherapy was 6% compared to 11% after TME surgery alone [4]. Based on these results, standard treatment in the Netherlands for T2-3 rectal cancer without threatened circumferential margin (CRM) or N2 stage is pre-operative short course radiotherapy followed by TME surgery. Long course chemoradiation therapy (CRT) is indicated for locally advanced disease.

In the majority of patients with rectal cancer a low anterior resection (LAR) with primary anastomosis will be performed. These patients have a risk of significant postoperative morbidity, such as anastomotic leakage, faecal (urge) incontinence, tenesmus and soiling. For patients with distal rectal cancer it is often impossible to preserve the sphincter and an abdominoperineal resection (APR) with a permanent colostomy must be performed. Quality of life in these patients was not proven to be worse than in patients who underwent a LAR [5].

### Neoadjuvant chemoradiation therapy

Patients with more advanced tumours are usually treated with a long course of CRT in order to facilitate tumour downstaging. Two multicenter randomised trials have demonstrated the benefit of additional chemotherapy to radiotherapy, leading to a higher complete response rate and a lower local recurrence rate after 5 years follow-up [6,7]. CRT can potentially increase the number of patients who undergo sphincter sparing surgery, although only few authors have demonstrated this in a prospective trial [8-10].

A pathological complete tumour response (pCR) following long-course CRT is reported in 8 - 27% of the patients [10-16]. Patients with a complete response have an improved overall survival and local recurrences in patients with ypT0 and ypT1 tumours are low (0% - 6%). The additional value of TME surgery in case of a pCR after CRT is questioning. The selection of patients with a pCR is difficult using imaging techniques and transanal excision of the remaining tissue or residual tumour is probably the most profound method.

### Local excision/TEM

Transanal local excision (LE) is performed in patients with benign and low-risk superficial malignant rectal neoplasms. Transanal endoscopic microsurgery (TEM) is a local excision technique which enables the surgeon to perform a full thickness excision with great precision. An operating rectoscope with a diameter of 4 cm and a length of 12 or 20 cm is used. The scope has four work channels, a stereo optic vision channel, a light source, and an insufflation port to obtain a pneumorectum for maximum exposure. TEM is superior to local excision according to Parks for benign and malignant rectal neoplasms. There is a significantly lower risk of irradical or incomplete resection and consequently a lower recurrence rate [17-19]. TEM is also considered an alternative for patients who are unsuitable for major surgery because of medical comorbidity or those patients who require an APR but refuse a colostomy. Unfortunately, local excision leads to higher rates of local recurrence and survival may be compromised compared to radical TME surgery except for low-risk T1 tumours [20,21].

### Lymph node involvement

The key to appropriate use of LE for rectal cancer is patient selection; accurate preoperative primary tumour staging and prediction of lymph node involvement. For detection of nodal disease, ERUS and MRI have a similar sensitivity (67% versus 66%) and specificity (78% versus 76%) [22]. However, both examinations are highly operator dependent. MRI provides excellent imaging of the rectum, mesorectum, fascia propria of the rectum, and other pelvic structures and is useful for determining the risk of CRM involvement preoperatively. These aspects are not relevant to early-stage patients considered for local excision. The risk of lymph node involvement increases with depth of invasion of the rectal wall. Even in patients with a T1 stage, there can be lymph node involvement. The incidence of lymph node metastasis ranges from 6% to 14% for T1 tumours, 17% to 23% for T2 tumours, and 49% to 66% for T3 tumours [23]. The percentage of patients with involved lymph nodes is much lower after neoadjuvant CRT [24,25], probably because CRT has sterilised tumour containing lymph nodes. Others have shown that there is a correlation between the T stage and the N stage after CRT [26-29].

This effect of neoadjuvant CRT enables a combined treatment modality with local excision.

## Methods/Design

### Hypothesis

Since 8% to27% of the patients receiving neoadjuvant CRT for locally advanced rectal cancer has a pCR [10-15], a rectum saving treatment should be achievable for a number of patients with distal rectal cancer. In the CARTS-study, patients will be treated with CRT aiming at reaching a (near) pCR. By excision of the primary tumour site by TEM patients with a pathological (near) pCR (ypT0-1) can be identified.

### Objectives

Primary objective of the study is to determine the number of patients with minimal residual disease (ypT0-1) after neoadjuvant CRT followed by TEM surgery. The resection specimen should be complete (> 2 mm margin) without evidence of nodal metastases (if nodes are found in the full thickness specimen). Secondary objectives are quality of life and local recurrence rate.

### Design

This study is a non-randomized feasibility study to determine whether radiotherapy combined with capecitabine followed by organ-sparing surgery using TEM can be considered as a valid new treatment modality in distal rectal cancer. The flow chart of the study is showed in Figure 1.

**Figure 1 F1:**
[figure not shown]
**flowchart of the CARTS-study**.

### Study population

Patients who meet the following inclusion criteria are eligible for participation in this trial: diagnosis of a distal adenocarcinoma within 10 cm of the anal verge, staged as cT1-T3 tumour on imaging, age > 18 years and written informed consent.

Exclusion criteria are: Low risk T1, tumour ineligible for TEM (circular or intra-anal tumour), pre-existing faecal incontinence (soiling is not), synchronous tumours, or presence of mesorectal lymph nodes larger than 5 mm on CT, MRI and/or endorectal ultrasound and contraindications for capecitabine.

### Participating centres

At least 15 Dutch hospitals will participate in this study, including 3 university medical centers.

### Interventions

#### Neoadjuvant chemoradiation therapy

All patients will receive neoadjuvant CRT, consisting of radiotherapy with a total dose of 50 Gy which is given in 25 fractions during 5 weeks. Patients will receive 825 mg/m^2 ^capecitabine b.i.d. 7 days per week during the whole treatment period. Six weeks after ending the CRT, therapy effect is evaluated by MRI, rectoscopy and ERUS. Patients with a clinical T0-2 tumour after CRT will undergo LE using TEM 8 - 10 weeks after the end of the neoadjuvant treatment. All other patients will undergo TME surgery.

After histological examination of the resected specimen, all patients with an ypT2-3 tumour, positive resection margins, or lymphangioinvasive growth, will undergo radical surgery within 4-6 weeks after the TEM-procedure.

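### No nodal finding after chemoradiation leads to TME: both the restaging rule and the list of triggers for radical surgery after TEM need a nodal condition

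*Protocol article*

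**What the plan says.** All references are to the protocol article.

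- **Entry.** The Abstract limits the trial to clinical N0 disease. Study population lists as an exclusion "presence of mesorectal lymph nodes larger than 5 mm on CT, MRI and/or endorectal ultrasound".
- **Restaging.** Under Neoadjuvant chemoradiation therapy: "Six weeks after ending the CRT, therapy effect is evaluated by MRI, rectoscopy and ERUS". The routing rule follows: "Patients with a clinical T0-2 tumour after CRT will undergo LE using TEM", 8 to 10 weeks after treatment ends, and "All other patients will undergo TME surgery".
- **After TEM.** The same section states that "all patients with an ypT2-3 tumour, positive resection margins, or lymphangioinvasive growth, will undergo radical surgery", within 4 to 6 weeks.
- **Endpoint.** Objectives requires a complete specimen with ypT0-1 disease, "without evidence of nodal metastases (if nodes are found in the full thickness specimen").
- **Rationale.** Lymph node involvement, in the Background, says that appropriate use of local excision depends on patient selection, meaning accurate T staging and prediction of nodal involvement. It adds that involvement is much lower after chemoradiation and that T and N stage are correlated after it.

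**The concern.** The routing rule is complete. One variable, clinical T stage, sends a patient to TEM, and the second sentence assigns all the rest. A patient who is clinical T0-2 at six weeks and has a new or enlarged mesorectal node is therefore sent to TEM, although the same node at entry would have kept that patient out.

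The specimen rule does not correct this. A tumour-positive node in the TEM specimen fails the endpoint under Objectives but is not on the list of reasons for radical surgery. A patient with ypT0-1, clear margins, no lymphangioinvasion and a positive node in the specimen would count as a failure and still keep the mesorectum.

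Two things are at stake. One is safety: TEM does not treat the mesorectum. The other is the meaning of the endpoint: a suspicious node seen on imaging usually lies outside the TEM specimen, so such a patient can count as a success. With at least 15 hospitals, an unwritten nodal rule may also be applied differently from centre to centre.

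**Working it through.** **1. Where nodal status acts**

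| Step | T stage used | Nodal status used | Consequence of a nodal finding |
|---|---|---|---|
| Entry (Study population) | yes | yes, larger than 5 mm | excluded |
| Six-week restaging | yes | no | none stated |
| TEM specimen, endpoint (Objectives) | yes | yes, if nodes are present | not a success |
| TEM specimen, further surgery | yes | no | none stated |

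Nodal status acts at entry and in the endpoint, but at neither of the two treatment decisions in between.

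**2. The planned design, reproduced**

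Inputs from Sample size calculation: failure rate 15%, success rate 30%, alpha and beta 0.1, looks at 20 and 33, total 55. The article gives no stopping boundaries. Among exact binomial designs with futility stops at these looks, the one that meets both error limits is: stop at 2 or fewer of 20, stop at 5 or fewer of 33, success at 12 or more of 55. It gives alpha 0.0985 and power 0.9006, so N = 55 is reproduced.

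(Primary outcome asks for more than 12 of 55, that is, 13 or more. In a single stage that has alpha 0.060 and power 0.882. This is a separate matter, but it explains why two thresholds appear below.)

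**3. Cost of a nodal rule**

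Let q be the share of would-be successes diverted to TME. The article does not give q; the values below are assumptions. True success rate = 0.30 × (1 − q).

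| q (assumed) | True rate | Power, 20/33/55, success at 12 or more | Chance of 13 or more of 55, single stage |
|---|---|---|---|
| 0 | 0.300 | 0.901 | 0.882 |
| 2% | 0.294 | 0.885 | 0.862 |
| 5% | 0.285 | 0.858 | 0.828 |
| 10% | 0.270 | 0.802 | 0.759 |

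**4. Why the nodal rule should not fire on either test alone**

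Lymph node involvement gives specificity of 78% for ERUS and 76% for MRI. If either positive test reroutes, and errors are independent of each other and of entry imaging, joint specificity is 0.78 × 0.76 = 0.593. About 41% of node-negative would-be successes would then be rerouted. The success rate becomes 0.30 × 0.593 = 0.178, and the chance of 13 or more of 55 is about 0.17. This is an extreme case, because every patient has already passed the 5 mm limit at entry, but it shows which form of the rule to avoid.

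**5. What the published node figures do and do not measure**

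The same section gives nodal involvement of "17% to 23% for T2 tumours, and 49% to 66% for T3 tumours". With sensitivity se, specificity sp and prevalence π, the share truly node-positive before chemoradiation among patients imaged as N0 is π(1 − se) / [π(1 − se) + (1 − π)sp].

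- ERUS (0.67, 0.78): 8.0% to 11.2% for T2; 28.9% to 45.1% for T3.
- MRI (0.66, 0.76): 8.4% to 11.8% for T2; 30.1% to 46.5% for T3.

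These describe occult disease before treatment, assuming the cited accuracy applies to the 5 mm criterion. They are not the share with a suspicious node at six weeks, which is the group the restaging change would touch.

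**The case against.** The strongest case on the other side has five parts.

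- **Few patients are affected.** Everyone entered without a node over 5 mm, and chemoradiation lowers involvement. Restaging catches only nodes that are new, have grown or were misread at entry. This stands, and it limits the benefit as well as the cost. A reader might infer from the percentages in step 5 that up to nearly half of T3 patients would be helped. The documents do not support that, because those figures measure occult disease before treatment.
- **A 5 mm cut-off is not validated after chemoradiation.** This stands. A reader might infer that the entry rule should be repeated as a hard limit on either test. The article gives no support for that, calls both examinations highly operator dependent, and aims to save the rectum.
- **Routing on T stage is reasoned.** The article cites a T-N correlation after chemoradiation. That supports offering local excision. It does not justify leaving a visible suspicious node, or a proven positive one, without consequence.
- **The gap may be closed elsewhere.** The text never says that nodes are ignored, the Abstract makes TEM depend on clinical response, and the Figure 1 flow chart is not shown. A nodal condition there would still conflict with the complete rule in the text, which would need correcting.
- **Follow-up is close.** Secondary outcome provides visits every three months and MRI and CT every six months for three years, with rectoscopy and ERUS every three months after successful TEM. This is a real safeguard, but it acts after the treatment decision.

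**Conclusion.** The point holds as a defect in the written treatment rules. After entry, no nodal finding leads to TME, although the article's own eligibility criteria, rationale and endpoint all treat nodes as decisive. The specimen trigger is the clearest part: a proven positive node should not leave the patient without radical surgery. The restaging condition is also warranted, as a judgement on MRI and ERUS together and not as a hard size limit.

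The number of patients affected cannot be calculated from the article and is probably small. The power losses in step 3 rest on assumed diversion shares and on stopping boundaries reconstructed from the stated error rates. N = 55 is not in question here.

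**What to change.** In Neoadjuvant chemoradiation therapy:

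1. Add a tumour-positive lymph node in the TEM specimen to the findings that lead to radical surgery. Such patients already fail the endpoint, so this costs no power.
2. Restate the restaging rule: TEM for clinical T0-2 without mesorectal nodes judged suspicious on the six-week MRI and ERUS read together, where suspicious means new, or grown beyond the 5 mm entry limit; TME for all others.
3. If the flow chart shows the routing, make it match.

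MRI and ERUS are already done at six weeks, so no extra imaging or reader is needed. The cost is that a few patients with false-positive nodes will have TME and cannot count as successes. At assumed diversion of 2% or 5%, power falls from about 0.90 to 0.885 or 0.86.

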#### TEM

TEM will be performed as described by Buess [30]. Under general/spinal anesthesia, a specialized TEM rectoscope of 12 or 20 cm in length (Wolf GmbH Knittlingen or Storz GmbH Tuttlingen, Germany) is inserted within the rectum to assure proper visualization of the lesion. The rectal cavity is insufflated with CO_2 _by a combined endosurgical unit to achieve constant distension for appropriate visualization of the rectal neoplasm. The combined endosurgical unit further regulates irrigation and suction, thereby maintaining a constant intrarectal pressure.

### Outcome parameters

#### Primary outcome

Primary objective of the study is to demonstrate that more than 12 of 55 patients have minimal residual disease 8 - 10 weeks after neoadjuvant CRT. Minimal residual disease is defined as an ypT0 or ypT1 stage.

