### Sample size calculation

Fifty-five patients will be included in this study. The study treatment protocol is considered successful if 30% or more of the included patients will complete CRT and undergo TEM surgery with complete resection of the ypT0-1 tumour. This means a resection with > 2 mm resection margin. A response of 15% or less will be considered a failure of this treatment modality. A three-step model for phase II cancer clinical trials will be used for calculating patient numbers with an alpha and beta of 0.1. An evaluation will be planned after 20 and 33 patients.

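### Requiring more than 12 of 55 successes does not give the stated beta of 0.1: power at 30% is at most 88%, and about 86% with the interim stops that fit the design; the design needs at least 12

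*Protocol article*

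**What the plan says.** Under Outcome parameters, Primary outcome, the protocol article states the aim of the trial as to "demonstrate that more than 12 of 55 patients have minimal residual disease". Read literally, 13 is the smallest positive result.

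The Sample size calculation section gives the design behind that number:

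- Size: "Fifty-five patients will be included in this study".
- Unacceptable rate: "A response of 15% or less will be considered a failure of this treatment modality".
- Target rate: the treatment is "considered successful if 30% or more of the included patients will complete CRT and undergo TEM surgery", with complete resection of a ypT0-1 tumour.
- Error rates: "A three-step model for phase II cancer clinical trials will be used for calculating patient numbers with an alpha and beta of 0.1".
- Interim looks: "An evaluation will be planned after 20 and 33 patients". The Abstract agrees: "A three-step analysis will be performed after 20, 33 and 55 patients".

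The article gives no interim stopping limits and mentions no early declaration of success.

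**The concern.** In a single-arm design with a count as the decision rule, the rates, sample sizes, interim limits and final cut-off together determine alpha and beta exactly. The article prints all of these except the interim limits, so the final cut-off can be tested against the stated beta. It looked one patient too high.

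The article's closing discussion says that a randomised phase III trial will follow if the protocol proves feasible, so this count is the go/no-go number. If the cut-off is too high, the risk of dropping a treatment that reaches the 30% target is larger than stated. A final result of exactly 12 of 55 would be positive under the design and negative under the printed rule. Correcting the number after such a result would look driven by the data.

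**Working it through.** **Inputs.** From Sample size calculation: p0 = 0.15, p1 = 0.30, alpha = beta = 0.1 (alpha taken as one-sided), N = 55, looks after 20 and 33. From Primary outcome: success if X ≥ 13. The stages therefore add 20, 33 − 20 = 13 and 55 − 33 = 22 patients.

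**Method.** All figures are exact binomial. With futility limits r1, r2 and final limit r3 (stop or conclude negative at or below the limit), let F1, F2, F3 be the probabilities of ending negative at each stage. They come from convolving the stage distributions and removing the stopped paths. Then P(success) = 1 − F1 − F2 − F3. This is alpha at p = 0.15 and power at p = 0.30.

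**Step 1: reproduce the design.** All futility limits at 20/33/55 were searched for alpha ≤ 0.1 and power ≥ 0.9. Exactly one set qualifies: r1 = 2, r2 = 5, r3 = 11, with success at 12 or more.

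- Alpha = 1 − 0.4049 − 0.2530 − 0.2436 = 0.0985
- Power = 1 − 0.0355 − 0.0245 − 0.0394 = 0.9006
- Expected size at 15% = 20 + 13 × (1 − 0.4049) + 22 × (1 − 0.4049 − 0.2530) = 35.26

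A wider search, with final sizes from 50 to 60 and free timing of the looks, also gave this as the qualifying design with the smallest expected size at 15%. The article's 20, 33 and 55 therefore come out exactly, with a final cut-off of at least 12.

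**Step 2: the printed cut-off without interim stops.** This is the most favourable case for power when the looks can stop only for futility.

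- Alpha = P(X ≥ 13 | 55, 0.15) = 0.060
- Power = P(X ≥ 13 | 55, 0.30) = 0.882, so beta = 0.118

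A futility stop can only remove paths that might have reached 13. So 0.882 is a ceiling for every choice of futility limits.

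**Step 3: the printed cut-off with the stops from Step 1.**

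- Alpha = 1 − 0.4049 − 0.2530 − 0.2866 = 0.0555
- Power = 1 − 0.0355 − 0.0245 − 0.0811 = 0.8589, so beta = 0.141

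**Step 4: are the stops needed with a cut-off of 12?** Without them, P(X ≥ 12 | 55, 0.15) = 0.113 and P(X ≥ 12 | 55, 0.30) = 0.933. Alpha exceeds 0.1, so a cut-off of 12 is valid only together with the interim stops.

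| Success rule | Futility stops | Alpha | Power | Beta |
|---|---|---|---|---|
| ≥ 12 of 55 | ≤ 2/20, ≤ 5/33 | 0.0985 | 0.9006 | 0.099 |
| ≥ 12 of 55 | none | 0.113 | 0.933 | 0.067 |
| ≥ 13 of 55 (as printed) | none | 0.060 | 0.882 | 0.118 |
| ≥ 13 of 55 (as printed) | ≤ 2/20, ≤ 5/33 | 0.0555 | 0.859 | 0.141 |

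**The case against.** **Early success.** The ceiling of 0.882 assumes looks that stop only for futility, and the article does not say that they do. If success could also be declared early, power could be higher. The best such design found that ends at 13 or more declares success at 7 of 20 or 9 of 33 with no futility stop. It has alpha 0.088 and power 0.898, so beta is 0.102. That is close to 0.1 but still misses it. It also would call a trial successful on 7 or 9 patients, which is not the printed rule. The assumption should be stated, but it does not rescue the figures.

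**Unprinted boundaries.** The stops at 2/20 and 5/33 are inferred. With lighter futility limits the printed cut-off has power 0.878 (1/20 and 4/33) or 0.882 (0/20 and 2/33). This stands: the 86% is conditional on the inferred stops, and the match with 20/33/55 is strong evidence of intent, not proof. The finding that beta exceeds 0.1 does not depend on them.

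**Different counts.** The primary outcome counts ypT0-1, while the 15% and 30% refer to the narrower outcome of completing chemoradiation and having a complete TEM resection. Read as an observed proportion, 30% or more would even mean 17 of 55, with power of about 49%. This stands as a further reason to word the rule once. No reading makes 13 of 55 deliver a beta of 0.1 at a 30% rate.

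**Size.** The slip is one patient and is conservative on alpha. The final decision changes only at exactly 12 of 55, which has a probability of about 5% at either rate without stops (0.051 at 30%, 0.053 at 15%). That is fair, and limits the practical effect.

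**Conclusion.** The concern holds. The printed cut-off and the printed beta contradict each other. With looks that can stop only for futility, power at 30% is at most 0.882 whatever the limits. With the only limits that fit the article's sizes and error rates, it is 0.859. Beta is then 0.141 against the stated 0.10, while alpha falls to 0.056. The sample size and looks are sound; the cut-off is one too high, most plausibly because 12 or more became more than 12.

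The 0.882 rests on the article's figures and on there being no early declaration of success. The 0.859 rests in addition on the inferred stops at 2/20 and 5/33.

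**What to change.** Check the full protocol's three-step boundaries, then make the Primary outcome and Sample size calculation sections agree in one of two ways:

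1. Replace more than 12 with at least 12 of 55, and state the interim rule that makes the error rates true: stop for futility at 2 or fewer successes in the first 20 or 5 or fewer in the first 33. The interim rule must accompany the cut-off, because 12 of 55 without stops has alpha 0.113.
2. If more than 12 is intended, keep it and restate the error rates as alpha about 0.06 and beta about 0.14 under those stops, or recompute them if the full protocol uses other limits.

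In either case, define the success being counted in the same words in both sections, and make clear that 30% is the design rate and not an observed threshold. The cost is one number and a sentence or two, with no extra patients. It should be done before outcome data are seen.

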After CRT, pCR has been reported in 8-27% of the patients [10-15]. This has led to evaluation of a wait and see strategy for patients with a clinical complete response (cCR), which is currently investigated for oncological safety by several investigators [42]. However, a pathological evaluation of the tumour remnant has several potential advantages to select patients for rectum sparing treatment. First of all, cCR is not always a pCR [42-45]. We have described a patient with a cCR, which demonstrated to be an ypT2 tumour after TEM, but eventually turned out to be a ypT3N1 tumour after TME surgery [45]. In these patients who seem to have a favourable response, a wait and see policy will delay adequate mesorectal excision. Secondly, a clinical partial response can be a pCR. In order to prevent patients with palpable tumour scarring from undergoing TME surgery, a biopsy of the scar seems to be the best option. Thirdly, patients with a near complete response after CRT (ypT1) can be adequately treated with a full thickness excision of the rectal wall.

The combination of TEM and CRT has been studied retrospective [46] and is studied in a similar protocol in the USA (ACOSOG Z0641 study) [47]. Local recurrence after a pCR (ypT0) has never been described, and also the local recurrence rate after a near complete response (ypT1) is reported to be low (0-6%). For ypT2 carcinomas, varying LRR have been described but are likely to be above 10% [46]. Despite these observations the ACOSOG Z0641 protocol prescribes a wait and see policy for ypT2 tumours [48]. We feel that this might not be an oncological save treatment and have therefore chosen to perform TME surgery in all patients with ypT2 and higher tumours and monitor long term outcome. Another interesting observation will be the registration of complications after TEM. In the case reports described in the literature, several patients experienced wound complications, but the exact rate will be established in this prospective analysis [49].

The trial accrual is expected to be adequate in the above mentioned centers and it is assumed that in two years all patients will be treated. This trial will give us an answer if this multimodality protocol for rectum saving treatment of rectal cancer is feasible and if so, a randomized phase III trial will be conducted.

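### The primary endpoint is defined in three non-equivalent ways, and the loosest wording stands beside the decision count, so success could be overstated against the 15%/30% benchmarks

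*Protocol article*

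**What the plan says.** The protocol article describes the primary endpoint in three sections of Methods/Design.

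- **Objectives**: ypT0-1 after CRT followed by TEM, with two further conditions: "The resection specimen should be complete (> 2 mm margin) without evidence of nodal metastases". The nodal condition applies only if nodes are found in the full-thickness specimen.
- **Primary outcome**: more than 12 of 55 patients must have minimal residual disease 8 to 10 weeks after CRT. The section then gives its own definition: "Minimal residual disease is defined as an ypT0 or ypT1 stage". It mentions no operation, margin, nodal status or completion of CRT.
- **Sample size calculation**: the protocol succeeds if at least 30% of included patients "will complete CRT and undergo TEM surgery with complete resection of the ypT0-1 tumour", with a margin above 2 mm; 15% or less is failure. No nodal condition appears. The design parameters stand here too: "A three-step model for phase II cancer clinical trials will be used for calculating patient numbers with an alpha and beta of 0.1".

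The section on neoadjuvant chemoradiation therapy sets the surgical routes. Patients who are clinically T0-2 after CRT have TEM at 8 to 10 weeks. For the rest: "All other patients will undergo TME surgery". After TEM, a ypT2-3 stage, positive margins or lymphangioinvasive growth leads to radical surgery.

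**The concern.** This is a single-arm go/no-go trial, and the Discussion makes a randomised phase III trial conditional on its result. That result is a count of successes, so one patient must be classified the same way wherever the endpoint is written. Here the only explicit count stands beside the loosest definition, while the benchmarks and error rates belong to a stricter one.

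If the loose definition is applied, patients whose rectum was removed, or whose excision was inadequate, could help to reach a threshold meant for complete TEM resection. The 10% limit on a false positive verdict would then not apply to the quantity of interest. Three wordings also leave room to choose the definition after the data are seen.

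**Working it through.** **1. The three definitions, by type of patient**

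| Patient with ypT0-1 | Objectives | Primary outcome (literal) | Sample size calculation |
|---|---|---|---|
| CRT completed, TEM, margin > 2 mm, no positive node | success | success | success |
| Direct TME | failure | success | failure |
| TEM, margin 2 mm or less | failure | success | failure |
| CRT completed, TEM, margin > 2 mm, positive node in specimen | failure | success | success |
| CRT not completed, TEM, margin > 2 mm, no positive node | success | success | failure |
| As the first row, but with lymphangioinvasive growth (referred to radical surgery) | success | success | success |

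Every success under either stricter wording is also a success under the literal Primary outcome wording. The literal rate is therefore equal to or higher than the strict rate, never lower. The two stricter wordings also differ from each other, in rows four and five.

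**2. Reproducing the design**

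Inputs from the Sample size calculation: "Fifty-five patients will be included in this study"; "An evaluation will be planned after 20 and 33 patients"; p0 = 0.15, p1 = 0.30, alpha = beta = 0.1. The article gives no interim boundaries and does not state sidedness. I assume a one-sided test and stopping for futility only.

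Let X20, X33 and X55 be cumulative successes, binomial with rate p. Success is declared with probability

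P(p) = Pr(X20 > r1, X33 > r2, X55 > r3).

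With looks at 20, 33 and 55, one boundary set meets both error limits: r1 = 2, r2 = 5, r3 = 11. It gives P(0.15) = 0.0985 and P(0.30) = 0.9006, so N = 55 reproduces.

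The article's own final rule is more than 12, that is r3 = 12. With the same interim boundaries, P(0.15) = 0.0555 and P(0.30) = 0.859. The mismatch between 11 and 12 is a separate matter; the figures below use the stated rule.

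**3. Effect of counting extra patients**

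Let the strict success rate be 0.15 and let a further fraction d of patients count only under the literal wording. The counted rate is 0.15 + d, and the chance of declaring success is P(0.15 + d). The documents give no value for d, so the range is assumed. The last column drops interim stopping, to show how little depends on the reconstructed boundaries.

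| Extra counted | Counted rate | P, 2/20 and 5/33, then > 12/55 | P, > 12/55, no interim stop |
|---|---|---|---|
| none | 0.150 | 0.0555 (5.5%) | 0.0603 |
| 1 percentage point (0.55 patients per 55) | 0.160 | 0.084 | 0.091 |
| 1 patient per 55 (1/55 = 0.018) | 0.168 | 0.114 | 0.123 |
| 2 per 55 (0.036) | 0.186 | 0.199 | 0.214 |
| 3 per 55 (0.055) | 0.205 | 0.308 | 0.328 |

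In both columns the planned 0.10 is passed between 0.55 and 1 extra patient expected per 55.

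**The case against.** The best defence is that the Primary outcome section is shorthand. It reuses a term that the Objectives section has already tied to TEM, and 8 to 10 weeks is the interval the article gives for TEM; it gives none for direct TME. The Abstract, Objectives and Sample size calculation all name TEM. The Sample size calculation also states a success criterion of its own, in strict form, beside the benchmarks.

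Much of this stands. The shorthand reading is reasonable, and the loose wording is not the only success criterion in the article. But the section does not refer back: it writes a self-contained definition and attaches the count to it. Even on the lenient reading, the two stricter sections still disagree on nodes and on completion of CRT.

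A reader might infer two stronger claims, and the documents support neither.

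- That the success rate is in fact overstated. This needs both the literal reading and at least one ypT0-1 patient who had direct TME or otherwise fails the strict conditions. Below about one such patient expected per 55, the error under the stated rule can stay within 10%.
- That the article itself reports ypT0-1 in TME specimens after restaging above T2. The Discussion says only: "Secondly, a clinical partial response can be a pCR". That is an argument for excising the scar so as to avoid TME. Many partial responders may be restaged T0-2 and have TEM. The route through direct TME is possible, but the documents do not say how often it occurs.

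**Conclusion.** The concern holds as an ambiguity with a known direction and an unknown size. The inconsistency is on the page and needs no assumption. The overstatement depends on reading the Primary outcome section literally; under that reading the rate cannot be lower than the strict rate.

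The margin is thin. Under the stated rule, the room between 5.5% and the planned 10% is used up by less than one extra patient expected per 55, and three would roughly triple the planned error. These figures rest on a true strict rate of 15%, reconstructed interim boundaries and an assumed number of extra patients. They show sensitivity and do not estimate what will happen. Because the trial's verdict is this one count, the wording should be settled before it is applied.

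**What to change.** Use one endpoint in the Abstract, Objectives, Primary outcome and Sample size calculation, tied to the 15%/30% benchmarks. A success is an included patient who completed CRT, underwent TEM, and has ypT0-1 with a margin above 2 mm and no tumour-positive node in the specimen. The denominator is all 55 included patients; everyone else counts as a failure, including those who go directly to TME or never reach surgery.

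Reconcile this with the section on neoadjuvant chemoradiation therapy by stating whether a ypT0-1 patient referred to radical surgery for lymphangioinvasive growth counts as a success. None of the three wordings settles this, and the definition above does not settle it either. Confirm as well that the benchmarks, which were stated without a nodal condition, are meant to apply with it. Report ypT0-1 regardless of operation as a secondary response rate.

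The cost is wording only, with no added patients or visits. The primary rate may be slightly less favourable than under the literal Primary outcome wording.
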